**Methods:**

This study is a randomized, mixed-methods, feasibility trial with 2 conditions. Older adults in the intervention condition will receive 1 hour of weekly technological assistance to send an email to a family member, for 8 weeks, with the assistance of a volunteer. Participants in the control condition will not receive any intervention. The primary outcomes are loneliness, measured using the University of California, Los Angeles Loneliness Scale, and depression, measured using the Center for Epidemiologic Studies Depression scale, both of which are measured weekly. Secondary outcomes are quality of life, as assessed using the Older People’s Quality of Life-Brief version, and technological literacy, evaluated using the Computer Proficiency Questionnaire-12, both of which will be administered before and after the intervention. Semistructured interviews will be completed before and after the intervention to assess participants’ social connectedness, familiarity with technology, and their experience with the intervention. The study will be completed in a long-term care facility in Southwestern Ontario, Canada. Significance was set at *P*<.05.

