### Study Design

This study is a mixed-method, randomized feasibility trial with 2 conditions. Participants in the intervention condition will receive assistance in sending an email to a designated family member once a week. This program will be carried out by experienced enTECH volunteers who have been trained in teaching older adults how to use technology. Participants in the control condition will continue interacting with their family as they do now (ie, not via information and communication technology). Participants in the control group also have access to 3 public computers in the facility and recreational therapists if they require support.

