### Outcomes

*Primary outcomes:* The primary outcomes of this study are loneliness and depression. Loneliness will be assessed using the UCLA Loneliness Scale-version 3 [43]. The scale is a 20-item measure using a 4-point Likert scale and has been validated for use with older adults [44]. Depression will be measured using the CES-D [45]; this is a 20-item scale, each with 4 response items ranked from 0 to 3 based on the frequency of symptoms associated with depression over the past week. A cut-off of over and equal to 16 has been used in multiple validation studies [46].

*Secondary outcomes*: The secondary outcomes of this study are quality of life and computer proficiency. Quality of life will be measured using the OPQOL-Brief and a 13-item Likert scale from 1 to 5. This scale has been validated in older adults [47]. Technological proficiency will be measured using the CPQ-12, a 12-item measure using a 1-5 Likert scale and has been well-studied in older adults [48].

*Feasibility outcomes:* The feasibility outcome measures of this study will include the number of participants that we are able to enroll in the study, adherence to the intervention (frequency of contact with the family and attendance to the program), and the rate of attrition [49]. We also intend to determine the challenges faced by the site and volunteers as a result of our intervention, in particular, the restrictions of having only university student volunteers as well as the restrictions of the daily schedules for the residents of the facility. These will both be determined quantitatively (eg, total number of participants, adherence) and qualitatively, where participants will be asked about their experiences with the program. We do not expect any adverse events as a result of our intervention.

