#### Secondary Outcomes

The OPQOL-Brief and the CPQ-12 will be analyzed by comparing changes in the scores between the intervention group and the control group. The normality of the data will be assessed using the Shapiro-Wilk test, and equality of the variances between the groups will be assessed via a Q-Q plot and the Brown-Forsythe test. The differences between prestudy and poststudy period assessments in the intervention and control groups will be assessed using pooled variances and a one-sided *t* test. If normality cannot be established or unequal variance is observed within the data, a Q-Q plot will be used to determine the appropriate test (eg, Sign test, Wilcoxon-Signed Rank Test, or Wilcoxon Rank-Sum Test). For all tests, statistical significance will be set at *P*<.05. Quantitative feasibility outcomes (eg, adherence and attrition) will be reported as descriptive data and compared using a one-sided *t* test or a nonparametric equivalent (Mann-Whitney *U* test). All evaluation outcomes will be integrated in a joint display.

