#### Power

This study was designed as a feasibility study for investigating the feasibility of a student-run initiative to reduce loneliness in older adults. A component of this study will be understanding recruitment and retention, which may have significant variability in our sample size. Based on previous studies on interventions to reduce loneliness in older adults, with an effect size of approximately 0.2 and alpha of .05 and 80% power, we expect our sample size to be 196 [43,50-54]. Accounting for attrition rates in other intergenerational programs would be approximately 10%, and the sample size would be 216 [20,55,56]. Since the nature of this study is a feasibility study, which we aim to use to guide a future randomized controlled trial, this feasibility trial is not registered.

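### Attrition and adherence are to be compared with a one-sided test whose direction is not stated; it can miss excess drop-out in one arm, and the attendance part of adherence has no control value to compare.

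*Protocol article*

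**What the plan says.** The Outcomes section lists the feasibility measures as the number enrolled, "adherence to the intervention (frequency of contact with the family and attendance to the program), and the rate of attrition". The analysis rule stands at the end of Secondary Outcomes in the Statistical Analysis section. It covers "Quantitative feasibility outcomes (eg, adherence and attrition" being the two examples given), which "will be reported as descriptive data and compared using a one-sided" t test "or a nonparametric equivalent (Mann-Whitney *U* test"). Just before this, the same paragraph sets the level: "For all tests, statistical significance will be set at *P*<.05". It does not say which arm is expected to do better.

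On the control arm, the Abstract states: "Participants in the control condition will not receive any intervention". Study Design adds: "Participants in the control condition will continue interacting with their family as they do now".

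The Power section explains why these outcomes matter: "A component of this study will be understanding recruitment and retention, which may have significant variability in our sample size". It also says that the study is to guide a future randomized trial. Its planning figures are 196, and 216 after attrition of about 10%.

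**The concern.** A one-sided test suits a question where only one direction is of interest. Differential attrition is not such a question. Controls are offered no programme yet complete weekly scales, so they may leave. Treated residents have weekly sessions that the Discussion expects to be hard to schedule, so they may leave too. Either imbalance would bear on the design of the later trial and on how far this trial's own group comparison can be trusted.

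Because no direction is named, a reader cannot tell which arm's excess would go unflagged, and the direction could be settled once the counts are known. The t test and the Mann-Whitney test are also awkward choices for a 0/1 outcome with 10 residents per arm.

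Adherence has a separate difficulty. One of its two parts is attendance at a programme that controls do not have.

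**Working it through.** **Inputs.** Planned enrolment is about 20, 10 per arm (Participant Recruitment), allocated 1:1 (Randomization and Blinding). The level is .05 (Secondary Outcomes). The planning numbers are 196, and 216 with about 10% attrition (Power). The attrition rates of 40% and 10%, and the result of 2 of 20 leaving, are assumptions for illustration; the article gives no arm-specific rates.

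**The plan's own figure.** 196 × 1.10 = 215.6, rounded up to 216. So the article inflates by multiplication. Division would give 196 / 0.90 = 217.8, or 218. No sample size in the article is tied to the feasibility comparison.

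**Step 1: what the one-sided test flags.** Code drop-out as 0/1, with a drop-outs in the suspected arm and b in the other. The pooled statistic is t = (a/10 − b/10) / √(s² × 2/10) on 18 degrees of freedom, where s² is the mean of the two sample variances. For a = 3, b = 0 the variances are 0.3 × 0.7 × 10/9 = 0.2333 and 0, so s² = 0.1167, t = 0.3 / 0.1528 = 1.96 and one-sided P = .033. Against b = 0 the test first rejects at a = 3; against b = 1, at a = 5; against b = 2, at a = 6.

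**Step 2: probability of a flag.** Sum the product of the two binomial probabilities over all 11 × 11 tables that reject:

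| True attrition | Aimed at the arm with more drop-out | Aimed at the other arm | Two-sided t | Two-sided Fisher |
|---|---|---|---|---|
| 40% vs 10% | 46.8% | 0.05% | 29.1% | 15.2% |
| 50% vs 10% | 65.5% | 0.01% | 47.1% | 29.5% |

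A one-sided Mann-Whitney test (normal approximation with tie and continuity corrections) gives the same 46.8% and 0.05% at 40% vs 10%, so switching to it does not help. As a single result, 5 of 10 versus 0 of 10 gives P = .996 in the wrong direction, against a two-sided Fisher P of .033.

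**Step 3: false-positive rate.** With equal true attrition of 10%, 20% or 30% in both arms, the one-sided t test rejects 2.5%, 4.6% or 5.0% of the time. With the direction fixed in advance, its size is therefore not inflated. If the direction is picked after seeing the counts, these rates double, to about 5.0%, 9.1% and 10.0%.

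**Step 4: choice of test, like for like.** At 3 versus 0 drop-outs:

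| Test | One-sided P | Two-sided P |
|---|---|---|
| t test | .033 | .065 |
| Fisher exact | .105 | .211 |

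The one-sided Mann-Whitney P is .038. On either row, sidedness accounts for a factor of two; the rest is the choice of test.

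**Step 5: adherence.** Attendance needs a programme. The Abstract and Study Design give controls none, so they have no attendance value. Frequency of family contact is different: controls keep their usual contact, so it can be compared if it is recorded in both arms.

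**Step 6: what an estimate would show.** If 2 of 20 leave, the exact (Clopper-Pearson) 95% interval is 1.2% to 31.7%. Applying the upper limit to 196 by the article's multiplication gives 196 × 1.317 = 258, against 216. By division it gives 196 / 0.683 = 287, against 218.

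**The case against.** The strongest reply is that description comes first. The sentence puts descriptive reporting ahead of the comparison, and Evaluation Outcomes promises a feasibility table. If drop-outs are tabulated by arm, 4 of 10 versus 1 of 10 is visible whatever the test says. This stands, and it rules out several stronger readings.

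- **That the plan offers only a test and wrongly omits an interval.** It does not offer only a test. An article may leave intervals to the table or to a fuller plan, so their absence is not in itself a fault.
- **That adherence cannot be compared at all.** Only attendance lacks a control value. The Week 8 text under enTECH Intervention and Study Procedure speaks of both groups finishing a last intervention session. This conflicts with the Abstract and Study Design and must be reconciled with them, but it does not describe a control programme.
- **That the t test inflates false positives.** With the direction fixed in advance, it does not (Step 3).
- **That the t test and Fisher differ as .033 does from .21.** That sets a one-sided value against a two-sided one; Step 4 gives the fair comparison.
- **That the planning number would move from 216 to 287.** That mixes two inflation formulas; Step 6 keeps them apart.

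A second reply is that no test does well with 10 per arm. This also stands: two-sided Fisher would miss 40% versus 10% about 85% of the time. It argues for estimating the rates and their difference, and gives no reason to keep a directional test.

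**Conclusion.** The point holds for what the article fixes: a one-sided comparison, with no direction, of an outcome where both directions matter. At 10 per arm and assumed attrition of 40% versus 10%, the chance of a flag is 46.8% or 0.05%, depending only on a choice that the article leaves open. The between-arm comparison of attendance has no content; that of family contact may have. These results rest on the planned 10 per arm, on a pooled t test of 0/1 drop-out, and on attrition rates that are assumptions.

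The consequence is limited to the feasibility conclusions and what they pass on to the later trial; the analysis of loneliness and depression is not affected. A reader might infer that differential drop-out would go unnoticed. The documents do not support that, since descriptive reporting is planned. What can mislead is the P value set beside it. The change is still worth making, because it is small and recruitment is to resume after the halt at 8 participants.

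**What to change.** Delete the one-sided test for feasibility outcomes. Replacement text could read: *Attrition will be reported overall and by arm with exact 95% confidence intervals, and the between-arm risk difference with a two-sided 95% confidence interval. Programme attendance will be summarised for the intervention arm only. Frequency of family contact will be compared between arms, two-sided, if it is recorded in both.*

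If a P value for attrition is wanted, use two-sided Fisher and state that its power is about 15% at 40% versus 10%. When the future trial is sized, set the inflation against the interval for attrition as well as the assumed 10%, and use one inflation formula throughout. Reconcile the Week 8 wording on control sessions with the Abstract and Study Design.

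The cost is one reworded sentence and a few exact intervals. Recording family contact in controls is extra work only if it is not already planned. The downside is that the reported precision will look poor, which is a fair picture of what 20 residents can show.

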#### Power

This study was designed as a feasibility study for investigating the feasibility of a student-run initiative to reduce loneliness in older adults. A component of this study will be understanding recruitment and retention, which may have significant variability in our sample size. Based on previous studies on interventions to reduce loneliness in older adults, with an effect size of approximately 0.2 and alpha of .05 and 80% power, we expect our sample size to be 196 [43,50-54]. Accounting for attrition rates in other intergenerational programs would be approximately 10%, and the sample size would be 216 [20,55,56]. Since the nature of this study is a feasibility study, which we aim to use to guide a future randomized controlled trial, this feasibility trial is not registered.

## Results

### Participant Recruitment

Recruitment started in November 2019. As of March 2020, we have recruited 8 participants. This study was halted as per the University of Waterloo Office of Research Ethics in accordance with public health guidelines. We expect that recruitment will be resumed once the long-term care facility can offer the program for older adults, in conjunction with approval from the ethics board to ensure safety for both students and participants. Gantt charts are provided detailing our progress to date Figure 2, which details our progress to date (Figure 2) and the expected timeline once permitted to resume (Figure 3).

**Figure 2 figure2:**
[figure not shown]
Gantt chart for currently completed pilot.

**Figure 3 figure3:**
[figure not shown]
Gantt chart for when the pilot will be restarted.

### Evaluation Outcomes

Demographic outcomes will be tabulated, as shown in Table S1 of Multimedia Appendix 9. A joint display will be used to integrate qualitative and quantitative data [57,58]. This joint display will present test statistics for the 4 variables measured as well as exemplary quotes from the intervention group before and after the study (Table S2 of Multimedia Appendix 9). There will also be a column to highlight the results of integrating the qualitative and quantitative data. Feasibility outcomes will be displayed, as shown in Table S3 of Multimedia Appendix 9.

## Discussion

### Overview of the Study

We were able to recruit 8 participants, before the study was forced to halt due to the COVID-19 pandemic, in accordance with institutional and public health guidelines. A large component of this study involves coordinating the schedules of student volunteers, older adults, and staff at the long-term care home. This presents a number of challenges as in-person classes lead to students generally being available only in the evenings, older adults often have busy schedules, and staffing shortages are prevalent in Canadian long-term care locations [59]. Scheduling is anticipated to be a problem, which will be resolved through extensive dialogue and trial-and-error scheduling. 

The enTECH Computer Club in this study is a club with the Waterloo Undergraduate Student Association (WUSA), which does not have the infrastructure to manage the awarded research funding. Additionally, club activities require approval from the WUSA. In consultation with WUSA, the decision was made to run this study independent of WUSA, so as to use existing university research infrastructure. The club was referenced to establish a basis for this study to indicate the program used and the expected backgrounds of the research assistants, but this does not indicate that the club is otherwise affiliated with this study.

### Principal Results

This study will contribute to a deeper understanding of intergenerational technology programs for older adults living in long-term care homes. We hope that these data will allow for stronger advocacy efforts for the benefits these programs can provide for older adults, especially in improving their mental health and reducing their feelings of loneliness. We also hope that this protocol will allow others who wish to study university club programs as a starting point on how to do so. Navigating the requirements for university clubs, which are generally affiliated with university student unions, as well as university research requirements, including institutional review board approval, is a first-time occurrence for our institution from our understanding.

### Limitations

Obtaining a sufficiently large sample to observe statistical significance for the measures used is anticipated to be a challenge, as resource limitations necessitate that this study is only run at 1 location. Should additional funding be secured, there is a potential for this study to be run at multiple sites.

### Conclusions

We hope that the results of this study will highlight the need for increases in innovative technologically focused programs for older adults and the need for additional resources to be directed to promoting the value of this program to older adults.

## Appendix

Multimedia Appendix 1 Location recruitment letter.

Multimedia Appendix 2 Advertisement to older adults.

Multimedia Appendix 3 Screening questions.

Multimedia Appendix 4 Email script for phone call with family member.

Multimedia Appendix 5 CONSORT 2010 flow diagram for the study.

Multimedia Appendix 6 Demographics questionnaire.

Multimedia Appendix 7 Preprogram interview guide.

Multimedia Appendix 8 Postprogram interview guide.

Multimedia Appendix 9 Proposed tables for recording evaluation outcomes.

## Abbreviations

CES-D: Center for Epidemiologic Studies Depression scale
CPQ-12: Computer Proficiency Questionnaire-12
OPQOL-Brief: Older People’s Quality of Life-Brief version
UCLA: University of California, Los Angeles
WUSA: Waterloo Undergraduate Student Association
